### Data management and analysis

Data will be imported into Stata V16. We will compare the proportion of children who completed IPT in both groups with statistical tests for small groups in an intention-to-treat approach, including all enrolled participants in the denominators. We will also compare the median number of weekly IPT pick-ups. We will compare the characteristics of caretakers, index cases, and children of the intervention and control arm. Missing data will be reported in descriptive tables. Medians and interquartile ranges will be calculated for continuous variables and proportions for categorical variables. Despite randomization, there may be confounding present regarding the probability of completing IPT. Potential confounders include the index case characteristics (sex, age, smear status), child characteristics (sex, age, kinship to the index case), caretaker’s characteristics (sex, age, kinship to the child, and to the index case, occupation, and education) the socio-economic status of the family and the health facility. To determine an unconfounded estimate of the effect of the intervention in the proportion of children who completed IPT, we will test models with a multivariate backward regression analysis. A saturated model with variables associated with IPT completion in our preliminary findings (smear status and treatment outcome of the index case, kinship and TST result of the child [14] and other variables associated (*p* < 0.1) with the outcome in the bivariate analysis will be tested against a model with variables with the weakest associations eliminated one by one. We will analyze the timing of the drop-outs (caretakers not coming back to pick up IPT) with Cox regression and the factors associated to that timing with a multivariate Cox regression analysis. We will report the proportion of enrolled to those eligible overall for the intervention group as well as per health facility, and we will report the full cascade of IPT (evaluation, prescription, initiation, completion) for the intervention and control facilities during the study period. As the data for the outcomes are routinely collected, we will follow the REporting of Studies Conducted using the Observational Routinely Collected Health Data (RECORD) statement to report the study findings [37].

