**Methods:**

An open-label, cluster-randomized superiority trial will be conducted in two districts in South Lima, Peru. Thirty health facilities will be randomized as clusters, 10 to the intervention and 20 to control (standard of care). We aim to recruit 10 children from different households in each cluster. Participants will be caretakers of children aged < 5 years old who initiated IPT. The intervention consists of educational material, and short message services (SMS) reminders and motivators. The primary outcomes will be the proportion of children who picked up > 90% of the 24 weeks of IPT (22 pick-ups) and the proportion of children who picked up the 24 weeks of IPT. The standard of care is a weekly pick-up with monthly check-ups in a health facility. Feasibility and acceptability of the intervention will be assessed through an interview with the caretaker.

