#### Power calculations

We expect to increase IPT completion from 30 to 70% with the intervention. A structured behavioral intervention that included self-monitoring and incentives to increase adherence to IPT among children increased IPT completion (OR 2.4, 95% CI 1.7–3.5) [36]. Our intervention will use incentives targeting children and two additional tools targeting the caretaker. Therefore, we expect to increase it by 3.5, the upper CI. In that scenario, the outcome would occur in 70% of the intervention arm. Considering an intra-cluster correlation coefficient of 0.38, we will need to recruit 8 children in each of the 30 clusters (10 intervention, 20 control), to be able to detect that difference with 80% power. Considering potential losses (e.g., children whose IPT is stopped for medical reasons), we will recruit 10 children per cluster. Therefore, we will enroll 100 children in the intervention clusters and 200 children in the control clusters. Sample size calculations were made in Stata v.12 (Stata Corp, 12.0, College Station, TX).

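### The analysis section names no method that accounts for facility clustering, although facilities are randomised and the sample size assumes an ICC of 0.38

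*Protocol article*

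**What the plan says.** The unit of randomisation is the facility. In the abstract's Methods: "Thirty health facilities will be randomized as clusters, 10 to the intervention and 20 to control". The Randomization section adds that facilities were first sorted into groups by TB caseload and number of children started on IPT, and that one intervention and two control facilities were drawn per group.

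The Power calculations section allows for clustering: "Considering an intra-cluster correlation coefficient of 0.38, we will need to recruit 8 children in each of the 30 clusters". Ten per facility are then recruited to cover losses, giving 100 and 200 children.

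The main comparison in Data management and analysis reads: "We will compare the proportion of children who completed IPT in both groups with statistical tests for small groups in an intention-to-treat approach". The same sentence puts every enrolled participant in the denominators. The section then plans:
- a comparison of the median number of weekly pick-ups;
- a backward-elimination regression for an unconfounded effect estimate;
- a drop-out analysis: "We will analyze the timing of the drop-outs (caretakers not coming back to pick up IPT) with Cox regression", followed by a multivariable Cox model.

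Facility has one stated role. It closes the list of potential confounders: "the socio-economic status of the family and the health facility". No analysis is said to allow for correlation between children of the same facility, and no significance level is given.

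**The concern.** Children attending one TB clinic share nurses, opening hours, stock and local practice, and the planning ICC says that their outcomes are strongly correlated. A test that counts 300 children as 300 independent observations understates the standard error, so differences between facilities can pass for an effect of the intervention. This bears on the primary superiority comparison, where a false-positive rate well above the nominal level would undermine a significant result.

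The regression does not repair this. Facility is not among the variables put into the starting model on the strength of preliminary findings. It therefore enters only through the bivariate screen at p < 0.1 and can be removed afterwards. Whether clustering is reflected at all would depend on a data-driven selection step, and retaining facility as fixed effects creates a different problem, shown below.

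**Working it through.** **Inputs.** From the protocol article: 10 and 20 facilities; 8 children required and 10 recruited per facility; ICC 0.38; completion 30% and 70%; power 80%. Assumed: two-sided alpha of 0.05, which is not stated.

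**1. The plan's own sample size.** For 70% against 30% with 1:2 allocation, the mean proportion is (0.7 + 2 × 0.3)/3 = 0.433. Without clustering, the intervention arm needs

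n1 = [1.96 √(1.5 × 0.433 × 0.567) + 0.842 √(0.21 + 0.21/2)]² / 0.4² = 17.3, so 18 children, or 21 with continuity correction.

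With m per facility the requirement is 10m / (1 + 0.38(m − 1)) ≥ n1, which gives m = 4 (n1 = 18) or m = 7 (n1 = 21). The stated 8 is not matched exactly but is on the safe side: at m = 8 the effective size is 80/3.66 = 21.9 and power is 88.7% uncorrected or 82.3% corrected. So the design pays for clustering heavily, with 80 intervention children where about 18 to 21 independent ones would do.

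**2. Analytic error of an unadjusted child-level test.** The design effect is DE = 1 + (m − 1) × ICC, and the false-positive rate is 2[1 − Φ(1.96/√DE)].

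- m = 10: DE = 1 + 9 × 0.38 = 4.42; √DE = 2.10; rate = 35.1%.
- m = 8: DE = 1 + 7 × 0.38 = 3.66; √DE = 1.91; rate = 30.6%.

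**3. Simulation check.** Beta-binomial data with no effect, 30% completion in both arms, 10 against 20 facilities, 10,000 runs, no stratification:

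| Children per facility | ICC | Chi-square | Continuity-corrected | Fisher | t-test on 30 facility proportions |
|---|---|---|---|---|---|
| 10 | 0.38 | 35.3% | 32.1% | 33.7% | 4.8% |
| 8 | 0.38 | 31.5% | 28.0% | 29.5% | 5.1% |
| 10 | 0.20 | 24.5% | 21.2% | 22.6% | 5.0% |
| 10 | 0.10 | 15.7% | 12.9% | 14.1% | 5.2% |
| 10 | 0.05 | 10.6% | 8.5% | 9.5% | 5.1% |

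**4. Effect of the grouped randomisation.** Per facility, the variance of the proportion is proportional to ICC + (1 − ICC)/m = 0.38 + 0.062 = 0.442 at m = 10, against 0.1 for independent children. If the groups removed 25% of the between-facility part (an assumption), this becomes 0.285 + 0.062 = 0.347, a ratio of 3.47 and a rate of about 29%. If they removed 50%, it becomes 0.252, a ratio of 2.52 and a rate of about 22%.

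**5. Facility as a fixed effect.** Every facility belongs to one arm, so the arm indicator equals the sum of the ten intervention-facility indicators. An intercept, arm and 29 facility indicators make 31 columns of rank 30, and the arm effect cannot be estimated.

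**6. Cox model.** An unadjusted score test gave about 37% in 3,000 runs, but only under an assumed exponential drop-out model. It is indicative and not a property of the planned analysis.

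**7. Power of a valid analysis.** For 30% against 70%, a t-test on the 30 facility proportions has simulated power of about 87% (m = 8) to 88% (m = 10).

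**The case against.** The text does not say that children are treated as independent, and no test is named. The small-groups wording may mean methods for few clusters: 100 and 200 children are not small groups, whereas 10 and 20 facilities are. The denominator clause can be read as explaining intention-to-treat, that is, who is counted; a facility-level proportion also has enrolled children in its denominator. The article condenses a fuller protocol, where a variance estimator might be named. Listing facility as a confounder could mean facility characteristics or a random effect and not indicator variables.

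Much of this stands. A reader might infer that the plan commits to an independent-children analysis with a 33% error rate throughout. The documents do not support that: the main test is ambiguous, the rate depends on the ICC, the cluster size and an assumed alpha, and it was derived for the unadjusted binary comparison alone. The collinearity result likewise applies only if facility enters as fixed effects.

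What does not fall away is that the section does more than stay silent. Its sentence speaks of the proportion of children and uses the word groups for the two arms, it names ordinary regression and Cox models, and it gives facility the role of a covariate open to elimination. That role is unsuitable for the unit of randomisation, whatever the main test turns out to be.

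**Conclusion.** The point holds in conditional form. The analysis section names no method that accounts for clustering in the primary comparison, the adjusted regression or the Cox models, although the design rests on it. If the primary comparison is run at child level, the false-positive rate of a nominal two-sided 5% test is roughly 28–35% at the planning ICC with 8–10 children per facility, falling to about 9% at ICC 0.05 with 10. These figures assume alpha of 0.05, equal facility sizes and no gain from the randomisation groups; a gain of the size illustrated would lower the rate but leave it well above 5%.

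A reader might also infer that the trial cannot support a superiority claim. That does not follow. Facilities are the randomised units, each child is enrolled through one of them, and a cluster-level test keeps about 87–88% power for the planned difference. The weakness lies in the stated analysis and can be corrected before the data are analysed.

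**What to change.** State one primary method that respects the unit of randomisation. Either:

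- compare the 30 facility-level completion proportions by a t-test, or by a permutation test that respects the randomisation groups (ten groups of three with one intervention facility each give 3^10 = 59,049 allocations), reporting a risk difference and a confidence interval on cluster-based degrees of freedom (30 − 2 = 28, or 30 − 10 − 1 = 19 if group effects are fitted); or
- fit a mixed or GEE model with facility as the cluster and a small-sample correction.

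State the significance level and sidedness. Apply the same clustering to the adjusted regression and the pick-up comparison, and use shared frailty or cluster-robust variance for the Cox models. Remove health facility from the confounders open to elimination; it belongs in the model as the cluster.

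The cost is wording in the protocol or analysis plan, with no extra recruitment. Confidence intervals become wider, by a factor of about 2.1 against a child-level analysis at ICC 0.38 and 10 per facility, which the sample size already allows for.

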#### Randomization

We will randomize 30 clusters — health facilities — 10 to the intervention and 20 to control. We aim to recruit 10 children from different households in each cluster. Twelve of the 48 health facilities were excluded from these classifications as they had less than 1 TB case notification per month. To randomize the 36 health facilities, we classified them into 11 groups: 10 groups of 3 health facilities and one group of six facilities based on the number of TB cases reported in 2018, and the number of children < 5 started on IPT in 2018 as registered in routine health information systems. The group with 6 health facilities had the smallest number of cases per year. To select 2 control facilities and 1 intervention facility, we randomly selected from the group with the highest burden (group 1) until reaching the 10 intervention and 20 control facilities. Only the group classification and not the name of the facility was visible during randomization. Random numbers were generated with the Excel formula Rand() next to each group for the 36 health facilities. A witness set the criteria to the assignment of health facilities from groups 1 to 10. After we completed the assignments, the names of the health facilities were unblinded and the list of intervention and control facilities was made public (Available at bit.ly/3FRTA01). There were three stand-by health facilities for both groups in case a replacement was needed.

Based on 2018 TB case notifications, in which each facility reported an average of 68 TB patients (index cases) per year, and each case has a mean of four household contacts, of which, on average one is < 5 years old and that ~ 10% of children would be non-eligible for IPT (Multidrug-resistant TB contact, contraindications to isoniazid, other) and that 30% of those eligible for IPT would not be started on it (as per our findings), we estimated that more than 150 children would be eligible for the study in 1 year.

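### The adjusted effect model starts from index-case treatment outcome, which is settled after enrolment, and selects its other covariates from the trial data

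*Protocol article*

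**What the plan says.** The protocol article, Data management and analysis, first plans an intention-to-treat comparison of completion with all enrolled participants in the denominators. It then warns of confounding despite randomisation and lists potential confounders, ending with "the socio-economic status of the family and the health facility".

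The adjusted model has a stated causal purpose: "To determine an unconfounded estimate of the effect of the intervention in the proportion of children who completed IPT". The method named for this is backward multivariable regression. The starting model holds four variables taken from preliminary findings, namely "smear status and treatment outcome of the index case, kinship and TST result of the child", together with "other variables associated (*p* < 0.1) with the outcome in the bivariate analysis". This model "will be tested against a model with variables with the weakest associations eliminated one by one". No retention threshold is given, and the text does not say that the arm term is protected from elimination.

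Under Randomization: "We will randomize 30 clusters — health facilities — 10 to the intervention and 20 to control".

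**The concern.** Three features of this procedure sit badly with its stated purpose.

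First, a variable that predicted completion in earlier observational work is not thereby a valid adjustment variable in a randomised comparison. If the intervention can change it, conditioning on it can take out part of the effect being estimated. Index-case treatment outcome is open to this; smear status is not.

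Second, choosing covariates by their association with the outcome, and then discarding the weakest, means that the model behind the adjusted effect is known only once the outcome data have been seen. The adjusted figure could then differ from the intention-to-treat figure because of the selection path alone.

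Third, every facility belongs to one arm. A facility term therefore cannot be handled like an ordinary confounder such as the child's age.

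At stake is how the adjusted result is read. It is presented as the estimate free of confounding, so readers may give it more weight than the unadjusted comparison.

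**Working it through.** The plan gives no figure for this model, so there is none to reproduce. The checks are of timing, algebra and scale.

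**1. Timing of index-case treatment outcome.** Under Standard of care, contacts are listed when the index case has recently been diagnosed; the child is then evaluated and prescribed IPT. Under Study participants, the prescription is an entry condition. The outcome of the index case's own treatment is therefore normally settled after the child has enrolled and the intervention has begun. The documents do not date it; this is an inference from those sections. Smear status, kinship and TST result belong to the diagnostic work-up and do not have this problem.

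**2. Route from intervention to that outcome.** Data collection plan allows the caretaker to be the index case. The educational material and reminders are addressed to the caretaker, so they could change that person's own treatment behaviour as well as the child's pick-ups.

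**3. Scale, under assumed values.** In a linear model with no unmeasured common cause of index-case outcome and completion:

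adjusted difference = total difference − b × δ

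Here δ is the intervention's effect on index-case treatment success, and b is the effect of that success on the child's completion. The total difference of 0.40 is the planned 70% minus 30% (Power calculations). The values of δ and b are assumptions.

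| δ | b | adjusted difference |
|---|---|---|
| 0 | any | 0.40 |
| 0.10 | 0.30 | 0.40 − 0.03 = 0.37 |
| 0.20 | 0.50 | 0.40 − 0.10 = 0.30 |

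**4. Selection.** The confounder list has 14 entries: 3 for the index case, 3 for the child, 6 for the caretaker, family socio-economic status, and facility. Removing smear status and the child's kinship (already in the starting model) and facility leaves 11. If all 11 were independent and unrelated to completion, the expected number passing p < 0.1 is 11 × 0.1 = 1.1, and the chance that at least one passes is 1 − 0.9^11 = 0.69. The content of the model is thus partly a matter of chance.

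To see whether this harms the test of the arm effect, a null simulation was run: 1000 runs, 30 facilities of 10 children, 30% completion in both arms, ICC 0.38, a linear probability model, 4 forced and 8 screened noise covariates, arm always kept, and a 5% retention rule assumed because the plan gives none.

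| Analysis | Type I error |
|---|---|
| Backward selection, clustering ignored | 36.5% |
| All covariates kept, clustering ignored | 35.3% |
| t test on facility proportions | 4.5% |

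Selection among noise covariates added 36.5 − 35.3 = 1.2 percentage points. The rest of the inflation comes from ignoring clustering, which is a different matter.

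**5. Facility.** A design matrix with an intercept, arm and 29 facility indicators (10 intervention and 20 control facilities) has 1 + 1 + 29 = 31 columns but rank 30. Arm is an exact combination of the facility indicators. With facility as fixed indicators, the arm effect cannot be estimated; with facility as a random effect, it can.

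**The case against.** The strongest reply is that this is a supplementary model. The intention-to-treat comparison stands apart from it and uses none of these covariates. That is correct: a reader might infer that the main result is compromised, and the documents do not support this.

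Other stronger readings also fail:

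- **The arm effect is bound to be inestimable.** The text does not mention indicators or fixed effects, and facility is not among the four named starting variables. The phrase can even be read as the socio-economic status of the facility, though a separate list item is the more natural reading. The point is conditional on the form of the term.
- **Selection makes the intervals clearly too narrow.** The simulation does not show this for noise covariates. What stands is that the estimate is not fixed in advance.
- **The intervention acts on index-case outcome by bringing the household to the clinic weekly.** Weekly pick-up is standard of care in both arms. The contrast is education, reminders and stories, so the route is indirect.
- **The variable is invalid simply because it is measured after randomisation.** Facilities were randomised first, so every child-level covariate is. The relevant test is whether the variable is settled after enrolment and open to influence by the intervention.
- **TST result is not collected.** Standard of care says that tests done to rule out TB are registered on the index-case card, and those cards are reviewed in both arms.

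It is also fair to say that an analyst would normally keep the arm term in a model built to estimate its effect. The text does not say so, however, and its elimination rule makes no exception.

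**Conclusion.** The concern holds in a limited form. The model meant to give an effect free of confounding is specified to start from a variable that is settled after enrolment and may respond to the intervention, and its remaining covariates are chosen from the outcome data. These are stated rules, not details left for later.

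The size of any bias is unknown. The 0.37 and 0.30 figures are illustrations that rest on assumed δ and b and on the absence of unmeasured common causes. If the intervention does not change index-case treatment outcome, this route contributes nothing. The plan cannot know that in advance, and omitting the variable costs the randomised comparison no validity.

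The facility point is a warning about how the term is entered. The point as a whole should be corrected, but it does not undermine the intention-to-treat comparison.

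**What to change.** For the adjusted effect estimate, specify one model in advance:

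- keep the arm term always;
- use a short set of covariates known at enrolment and available from the treatment card in both arms: index-case smear status, sex and age; child sex and age; kinship. The article describes the caretaker interview only for the intervention arm, so covariates drawn from it are less safe;
- add the randomisation group;
- remove index-case treatment outcome;
- let health facility enter only as the cluster, through a random effect or a cluster-level analysis.

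Backward selection, with treatment outcome among the candidates if wanted, can remain as a separate exploratory analysis of predictors of completion, labelled as such.

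The change is one of analysis wording and needs no new data. It costs slightly less flexible modelling. Entering the ten randomisation groups as a factor also uses degrees of freedom at facility level: 30 − 10 − 1 = 19 remain, against 30 − 2 = 28 with arm alone. Trial status puts the end of follow-up in June 2023, after the article's publication in January 2023, so the change could still precede the final analysis.
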